### **3.7 Data Collection and management**

Participants' data are pseudo-anonymized by assigning a unique code to each participant. Data pertaining the participants' information, video reviews, and the outcomes investigated in the trial, is recorded using pseudo-anonymized CRFs. Completed CRFs are checked for completeness and accuracy by the principal investigators.

All CRFs data is securely stored in electronic databases created using REDCap (Research Electronic Data Capture), a browser-based, metadata-driven software solution and workflow methodology used to design clinical and translational research secure password protected databases (REDCap, Vanderbilt University, Nashville, TN, USA).[56] Only the principal investigators and the study statistician will have access to the final trial dataset.

Data will be analysed by the study statistician ([name]) who will be blinded to group allocation coding.

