## 1. ABSTRACT

**Introduction:** Paediatric cardiac arrest (PCA), despite its low incidence, has a high mortality. Its management is complex and deviations from guideline recommendations occur frequently. We developed a new interactive tablet app, named PediAppRREST, to support the management of PCA. The app received a good usability evaluation in a previous pilot trial. The aim of the study is to evaluate the effectiveness of the PediAppRREST app in reducing deviations from guideline recommendations in PCA management.

**Methods and analysis:** This is a multicentre, simulation-based, randomized controlled, three-parallel-arm study. Participants are residents in Paediatric, Emergency Medicine, and Anaesthesiology programs in Italy. All 105 teams (315 participants) manage the same scenario of in-hospital PCA. Teams are randomized by the study statistician into one of three study arms for the management of the PCA scenario: 1) an intervention group using the PediAppRREST app; or 2) a control group (CtrlPALS+) using the Paediatric Advanced Life Support (PALS) pocket reference card; or 3) a control group (CtrlPALS-) not allowed to use any PALS-related cognitive aid. The primary outcome of the study is the number of deviations (delays and errors) in PCA management from PALS guideline recommendations, according to a novel checklist, named c-DEV15plus. The c-DEV15plus scores will be compared between groups with a one-way ANOVA model, followed by the Tukey-Kramer multiple comparisons adjustment procedure in case of statistical significance.

**Ethics and dissemination:** The Ethics Committee of the University Hospital of Padova, coordinating centre of the trial, deemed the project to be a negligible risk study and approved it through an expedited review process. The results of the study will be disseminated in peer-reviewed journals, and at national and international scientific conferences. Based on the study results, the PediAppRREST app will be further refined and will be available for download by institutions/health care professionals.

**Trial registration number:** NCT04619498

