### **3.3 Randomization, allocation concealment, and blinding**

Participants are randomized by the study statistician in teams of three, stratified by study site and residency program specialty. Randomization is conducted assuring that in every team there will be at least one PALS-certified team member assigned to the role of team leader. The same statistician assigns a unique team identification number to each team and prepares the list of participants associated with each team to be sent to the principal investigators. Participants are randomly divided in teams of three members per each scenario; the team leader is selected among PALS-certified residents whereas the other two members have to be at least BLS-certified. The teams are randomized with a 1:1:1 ratio in the intervention arm (PediAppRREST arm) and the two control arms.

The statistician also creates opaque sealed envelopes externally marked with the team identification number and containing a paper slip, which indicates the arm allocation for that specific team. Team group allocation is concealed until the simulation sessions. Randomization of participants to teams, and teams to the arms, is performed with SAS 9.4 (SAS Institute Inc., Cary, NC, USA) for Windows.

Due to the nature of the cognitive support tools used in the trial, blinding of participants as well as of research staff involved in the simulation sessions and video reviewers, is not possible. However, blinding of the statistician performing data analysis will be ensured. Data analysis is expected to be finalized by February 2022.

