After the scenario, all participants complete a demographic survey reporting their sex, age, year and type of residency program, experience in simulation and resuscitation, and time from PALS/P-BLS/BLS/ALS/ACLS certification. In addition, all the team leaders complete the NASA-TLX and the team leaders in the intervention arm also evaluate the app usability, by completing the SUS. Subsequently, all participants participate in a 15-minute debriefing during which they receive feedback about their performance, and the teams in the intervention arm are able to provide feedback about the app. During this phase, the debriefer reports the feedback received on the app in a specific CRF.

The videos of the scenarios will be evaluated by two independent, and previously trained, reviewers expert in paediatric emergency medicine and simulation. Training of the reviewers, on

RCT-unrelated PCA simulation videos, will be conducted by the principal investigator (FC), until the reviewers will reach at least 80% inter-rater agreement with the principal investigator. No more than two weeks will lapse between the training and the assessment of the RCT videos. The reviewers will use a standardized data collection form where actions performed by the team and time to performance will be assessed and recorded. Disagreements between reviewers will be resolved by consensus with a third independent reviewer, expert in paediatric emergency medicine and simulation. Inter-rater reliability between reviewers will be monitored and reported. Data pertaining the CPR quality from the manikin software will be extracted and recorded on a specific CRF. The scores on the c-DEV15plus, and all the secondary outcomes will be calculated by outcome assessors based on the data coded and reported by the video reviewers on the CRFs.

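### The protocol promises a blinded analysing statistician, but the same role title generates the team-to-arm allocation, and app-only data would identify the app arm; no step that would keep the analyst blinded is stated

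*Protocol*

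**What the plan says.** On allocation, the Protocol Abstract states: "Teams are randomized by the study statistician into one of three study arms". Section 3.3 agrees: "Participants are randomized by the study statistician in teams of three, stratified by study site and residency program specialty". It adds that the same statistician numbers the teams and draws up the roster for each team. It continues: "The statistician also creates opaque sealed envelopes externally marked with the team identification number", with a slip inside giving the arm.

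On blinding, section 3.3 accepts that participants, session staff and video reviewers cannot be blinded, but says that "blinding of the statistician performing data analysis will be ensured". Section 3.7 has the data analysed by the study statistician, "who will be blinded to group allocation coding", and limits access to the final dataset to the principal investigators and the study statistician.

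On app-only data, section 3.6 says that "the team leaders in the intervention arm also evaluate the app usability, by completing the SUS". It also has app feedback from the debriefing entered on a form of its own. Section 3.7 sends all case report form data to REDCap databases.

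**The concern.** An analyst is blinded only if the arm cannot be recovered from the data and records that the analyst holds. The protocol leaves two ways to recover it. One is the team number, which the study statistician linked to an arm when preparing the envelopes. The other is data that only one arm can produce.

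This matters because no other blinding is claimed. The claim is likely to be repeated in the publication as a safeguard, and readers would give it weight because everyone else is unblinded. Section 3.8.2 also leaves some choices until the data have been seen: which summaries to report, whether and how to transform, and who belongs to the per-protocol set. A blinded analyst is meant to protect exactly such choices.

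**Working it through.** No power, error rate or effect size enters this point, so there is no figure of the plan to reproduce. The check sets the role statements side by side and asks what an analyst could infer from the data.

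**1. Who does what**

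| Task | Role named | Protocol section |
|---|---|---|
| Randomise teams to arms | study statistician | Abstract |
| Randomise participants to teams | study statistician | 3.3 |
| Issue team numbers and team rosters | the same statistician | 3.3 |
| Prepare numbered envelopes holding the arm | the statistician | 3.3 |
| Hold access to the final dataset | principal investigators and study statistician | 3.7 |
| Analyse the data, blinded | study statistician | 3.7 |

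The title is singular throughout. No section names a second statistician, an independent holder of the allocation list, or a step that replaces team numbers before analysis.

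**2. Route through the team number.** The mixed model in section 3.8.2 treats the team as the cluster, so the analysis file needs a team identifier. Suppose that identifier is the number issued at randomisation and the analyst issued it. An A/B/C code in the arm column can then be decoded for every team. With 35 teams in each of three arms (section 3.8.1), that is 3 × 35 = 105 planned teams. This figure depends on both conditions: one person in both roles, and unchanged team numbers.

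**3. Route through app-only fields.** Sections 3.4.2 and 3.6 collect SUS only from team leaders in the app arm, and the app-feedback form can have content only for app teams. If either is in the analysis file, the code with non-missing values is the app arm: 35 of 105 planned teams. The other 105 − 35 = 70 teams have none of these fields, so this route does not tell the two control arms apart. It works even if the analyst never saw the allocation list.

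**4. What an unblinded analyst could influence.** The primary comparison is named in the Abstract and section 3.8.2: one-way ANOVA of the c-DEV15plus score, then Tukey-Kramer if significant. The open choices lie mostly elsewhere:

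- Mean or median concerns descriptive summaries, with a Shapiro-Wilk check stated.
- The transformation appears in the mixed-model paragraph. It is triggered by non-normal residuals, and its form is not fixed.
- The per-protocol set is named but not defined, and an intention-to-treat analysis is promised beside it.

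**The case against.** The strongest reply is that one person in both roles is an inference. It rests on the shared title. The analyst's name is masked, and the section on authors' contributions in the contents list was not in the text available for this review. Section 3.3 also speaks of the statistician who performs the data analysis, which is compatible with a second person. This stands. A reader might infer that the analyst certainly knows all 105 allocations, or that analysis blinding certainly does not exist. The document does not support that. It shows that the roles are not separated and that no mechanism for blinding is given.

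A second reply is that SUS is not among the outcomes compared between arms in section 3.8.2, and that nothing puts it in the file used for the primary analysis. Export content and order of release may be set in a statistical analysis plan or data management plan. This also stands, so the second route is conditional. It does not remove the point: section 3.7 gives the study statistician access to the final dataset, and the protocol asserts the blinding as settled.

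A third reply is that blinding is not the only defence against bias. Allocation is concealed until the session. Two trained reviewers work independently, with an agreement threshold in training and a third reviewer for disagreements. The tablet footage is kept from them, and CPR quality comes from the manikin software. All of this is right. Analyst blinding is the only blinding claimed, not the only protection.

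A reader might extend the point to the outcome assessors, for whom no blinding is promised. The protocol is silent there rather than wrong. Their task is largely mechanical scoring of actions and times already coded by unblinded reviewers, so this is not part of the point.

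**Conclusion.** The concern holds in a limited form. The protocol presents analyst blinding as assured, while its own division of tasks, as written, does not deliver it. The first route assumes that the shared title means one person and that team numbers are carried into the analysis file. The second assumes that SUS or app-feedback data are in that file, and it reveals the app arm only.

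The likely bias is modest and cannot be sized from the document. The primary test is fixed, people other than the statistician code and score the outcome, and the open choices bear mainly on summaries, the mixed model and the per-protocol analysis. Allocation concealment is not in question. The claim should be made true or withdrawn before the results are analysed and reported.

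**What to change.** Amend Protocol sections 3.3 and 3.7 in one of three ways.

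1. **Separate the roles.** State that someone other than the analyst generates and holds the allocation list. If two people already do this, one sentence is enough. If the analyst has already generated the list, the analysis would have to pass to someone else. SUS and app feedback should still be withheld, because separating the roles does not close that route.

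2. **Keep one statistician and build in the masking.** Lock and date the complete analysis program before any c-DEV15plus data are released. Run it on an export re-keyed by an investigator, with new random team codes and arms labelled A, B and C. Withhold SUS and app-feedback fields until the primary result is signed off. Locking the program is the stronger half of this option: the statistician also holds the team rosters, so re-keying alone may not fully hide the arms.

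3. **Withdraw the claim.** Delete the blinding statements and report the analysis as unblinded.

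The second option costs an export step, some wording and a slightly later SUS analysis. It needs no extra staff, since the principal investigators already have access to the final dataset. The third costs only wording.

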### **3.8 Statistical Analysis**

#### ***3.8.1 Sample size calculation***

We calculated sample size on the basis of the results obtained during the previous observational simulation-based study and the pilot study that tested the app usability.[37,38] Based on the preliminary results from these studies, using a single factor ANOVA model, 29 scenarios per each of the three groups (PediAppRREST, CtrlPALS+, CtrlPALS-) are necessary to detect a difference of at least 3.00 points on the c-DEV15plus scale using the Tukey-Kramer

(Pairwise) multiple comparison procedure at a 5% significance level and 80% power. The common standard deviation within a group is assumed to be 2.20.

In consideration that some possible technical problems with video-recording or other study procedures could occur, we aim to increase the recruitment of participating teams by 20% per arm, to compensate for loss of statistical power due to a potential insufficient sample size. Hence, we plan to have 35 scenarios per arm, for a total of 105 scenarios, which will include overall 315 residents divided in teams of three.

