### **3.8.2 Data analysis plan**

The results will be summarized for each study group with counts and percentages for categorical variables, mean and standard deviation (SD) or median and interquartile range for quantitative variables, as appropriate. The normality of the quantitative variables will be checked with the Shaphiro-Wilk test.

The c-DEV15plus scale, the performance and time to accomplish specific resuscitation interventions, NASA-TLX, CPT and cardiopulmonary resuscitation metrics will be compared between groups with one-way ANOVA model, followed by the Tukey-Kramer multiple comparisons adjustment procedure in case of statistical significance.

The outcomes will also be analysed with a linear mixed model considering the team as a cluster to evaluate the influence of participants' characteristics on the outcome. To take into account the correlation of the observations within a team, we will specify an undetermined correlation matrix. In case of a not normal distribution of the model residuals, we will proceed with a transformation in order to normalize the distribution.

Both intention-to-treat and per-protocol analyses will be performed.

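### The stated inputs need 12 teams per group for 80% power, not 29; at 29 per group, power for 3.00 points is 99.7%, and the basis of the 29 should be stated

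*Protocol*

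**What the plan says.** All the inputs are in Protocol section 3.8.1. The model and size are given as "using a single factor ANOVA model, 29 scenarios per each of the three groups", and these teams "are necessary to detect a difference of at least 3.00 points on the c-DEV15plus scale using the Tukey-Kramer" method. The error rate and power follow: "Pairwise) multiple comparison procedure at a 5% significance level and 80% power". The variability is fixed in one sentence: "The common standard deviation within a group is assumed to be 2.20". The section attributes the calculation to an earlier observational simulation study and the pilot study of the app.

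To allow for technical losses, "we aim to increase the recruitment of participating teams by 20% per arm", which leads to the final size: "Hence, we plan to have 35 scenarios per arm, for a total of 105 scenarios". Section 3.3 sets equal allocation: "The teams are randomized with a 1:1:1 ratio in the intervention arm". The analysis in section 3.8.2 is a one-way ANOVA, "followed by the Tukey-Kramer multiple comparisons adjustment procedure in case of statistical significance".

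The section does not give a pattern of group means, does not say whether power is per pair, for any pair or for all pairs, and does not mention the width of confidence intervals.

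**The concern.** A difference of 3.00 with an SD of 2.20 is a standardised difference of 3.00/2.20 = 1.36. That is very large, and 29 per group looks far too many for 80% power, even after a three-group multiplicity adjustment. If so, the section's stated difference, SD, power and sample size cannot all be right together.

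What is at stake is the description of the design, not its adequacy. Section 3.8.1 is the only place that says what the trial is powered for. A reader will take 3.00 points as roughly the smallest difference the trial can reliably detect. If n and SD are right, that difference is below 2 points. If instead 3.00 and n are right, the SD behind the calculation was not 2.20. The reader cannot tell which.

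**Working it through.** **Inputs** (Protocol sections 3.8.1 and 3.3): k = 3 groups, equal allocation; difference δ = 3.00; SD σ = 2.20; familywise α = 5%; target power 80%; stated n = 29 per group, raised to 35.

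**Formula.** For one pairwise Tukey-Kramer comparison with n per group:
- standard error of a difference: SE = σ√(2/n)
- degrees of freedom: 3(n − 1)
- critical value: c = q(0.95; 3, 3(n − 1))/√2, where q is the studentized range quantile
- power: the probability that a noncentral t with noncentrality δ/SE exceeds c

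**Attempt to reproduce the plan's figure.**

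| n per group | SE | c | δ/SE | Power for 3.00 |
|---|---|---|---|---|
| 11 | 0.938 | 2.465 | 3.198 | 76.4% |
| 12 | 0.898 | 2.454 | 3.340 | 80.7% |
| 29 | 0.578 | 2.386 | 5.193 | 99.7% |
| 35 | 0.526 | 2.378 | 5.705 | 99.95% |

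The smallest n reaching 80% is 12. The stated 29 is 29/12 = 2.4 times that.

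**Other readings that keep 3.00 and 2.20.** Sample size per group:

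| Reading | n |
|---|---|
| Unadjusted two-sample comparison, 80% power | 9 |
| Bonferroni for three pairs, 80% power | 12 |
| Overall ANOVA F test, means 0/1.5/3 | 12 |
| Overall ANOVA F test, means 0/0/3 | 9 |
| App differs from both controls (means 0/3/3) | 15 |
| All three pairs significant (means 0/3/6) | 16 |
| Tukey per pair, 90% / 95% / 99% power | 16 / 19 / 25 |
| Tukey per pair, 80% power, α = 1% / 0.1% | 17 / 24 |

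None reaches 29. A pattern in which the app's second contrast is only about 1.9 points could give roughly 29 (a second contrast of 2.0 gives 26, one of 1.5 gives 45), but that contradicts a difference of at least 3.00.

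**What 29 and 35 do deliver.** Solving the same formula for δ at 80% power with σ = 2.20:
- n = 29: δ = 1.87
- n = 35: δ = 1.70

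Solving instead for σ with δ = 3.00 and n = 29 gives σ = 3.53.

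**A criterion that does return 29.** Take the probability that the simultaneous 95% Tukey intervals all cover the true differences and also have half-width cS√(2/n) of at most 1.5 (total width 3.00), where S is the estimated SD. By simulation with σ = 2.20 this is 77.3% at n = 28 and 83.3% at n = 29, so 29 is the first n above 80%. Half-width alone already passes 80% at n = 28 (81.9%), so the match is specific to the joint criterion.

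**Inflation.** 29 × 1.20 = 34.8, rounded to 35; 3 × 35 = 105 teams; 105 × 3 = 315 residents. These steps follow from the stated 20% increase.

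**The case against.** The strongest defence is that 29 is not a miscalculation. Exactly the stated inputs (three groups, 3.00, 2.20, Tukey, 5%, 80%) return 29 if the 80% refers to joint coverage and narrowness of the simultaneous intervals, so the number may be sound and only its description poor. This is plausible, but it does not rescue the sentence. Section 3.8.1 speaks of power to detect a difference and never mentions interval width, and as a power statement it is false. The match is also not proof: the supporting studies and software output are not in the document, and an SD of about 3.5 or a difference of about 1.9 would give 29 just as well as a power calculation.

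The second defence is that little follows. That largely stands. The discrepancy is in the safe direction, the analysis in section 3.8.2 does not use the 3.00 figure, and no patients are exposed in a simulation study.

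Three stronger readings are tempting. A reader might infer that the interval criterion is how the trial was sized; the protocol does not say so. A reader might infer that the SD of 3.53 shows the 2.20 to be mistyped; it is only the value that would reconcile the other inputs. And a reader might infer that, because differences well under 3.00 can be significant, results should be judged against 3.00. The protocol never calls 3.00 a minimal important difference, and in any design with more than 50% power the smallest significant difference lies below the design difference.

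**Conclusion.** The point holds as an error in the stated sample-size justification. With three equal groups, SD 2.20 and Tukey-Kramer at 5%, 29 teams per group are not necessary for 80% power at 3.00 points; 12 are enough. The stated 80% is in fact 99.7% at 29 and 99.95% at 35, and the differences detectable with 80% power are 1.87 and 1.70 points.

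This rests on the usual per-pair definition of power and a roughly normal score with common SD. The choice of definition does not explain the gap: requiring significance against both controls needs 15 per group, and for all three pairs 16.

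The error is conservative. It does not make the trial underpowered for 3.00 under SD 2.20, and it does not invalidate the planned tests. The document does not settle which element is wrong: the difference, the SD, or the description of the criterion. It should be corrected, but it is not a fault that threatens the trial.

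**What to change.** Keep 105 teams. In section 3.8.1, replace the power sentence with one that holds, for example: with SD 2.20 and Tukey-Kramer at 5%, 29 evaluable teams per arm give 80% power for a pairwise difference of about 1.9 points (about 1.7 with 35 per arm) and more than 99% power for 3.0 points.

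The sponsor should also go back to the original calculation and state what produced 29. The candidates are:
- at least 80% probability that the simultaneous Tukey intervals cover and have half-width of at most 1.5 points;
- a power calculation with an SD of about 3.5;
- a power calculation with a difference of about 1.9.

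Whichever it is, correct the stated input or the description to match. If an input changes, recompute the power figures above with it. Do not write the interval criterion into the protocol unless the sponsor confirms it, and do not add a rule for judging results against 3.00.

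The cost is a wording change and a look at the original calculation. Recruitment, randomisation and analysis are unaffected.
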